**Table S1. Characteristics of entire study cohort (all patients recruited for participation).**

| Baseline characteristic [units]  | Overall            | Completed study    | Did not complete study | P-value |
|----------------------------------|--------------------|--------------------|------------------------|---------|
|                                  | n=65               | n=41               | n=24                   |         |
| Age [years, mean (SE)]           | 46.1 (1.33)        | 46.4 (1.7)         | 45.6(2.0)              | 0.773   |
| Sex [male n (%)]                 | 52 (80.0)          | 32 (78.0)          | 20 (83.3)              | 0.607   |
| Ethnicity [n, (%)]               |                    |                    |                        |         |
| White                            | 52 (80)            | 32 (78.0)          | 20 (83.3)              | 0.450   |
| Asian                            | 2 (4.9)            | 2 (4.9)            | 1 (4.2)                |         |
| Black                            | 6 (9.2)            | 3 (7.3)            | 3 (12.5)               |         |
| Other                            | 4 (6.2)            | 4 (9.8)            | 0 (0)                  |         |
| Cirrhosis [n (%)]                | 20 (30.8)          | 9 (22.0)           | 11(45.8)               | 0.044   |
| Decompensated cirrhosis [n (%)]  | 13 (20)            | 6 (14.6)           | 7 (29.3)               | 0.157   |
| Ascites [n (%)]                  | 8(12.3)            | 3(7.3)             | 5(20.8)                | 0.134   |
| HE [n (%)]                       | 0                  | 0                  | 0                      |         |
| ALT [IU/L, median (IQR)]         | 49.0 (30.2, 105.0) | 53.0 (32.2, 119.7) | 48.5 (27.2, 84.0)      | 0.435   |
| AST [IU/L, median (IQR)]         | 59.0 (30.2, 93.7)  | 58.5 (28.7, 100.2) | 64.0 (37.2, 87.0)      | 0.936   |
| ALT/AST                          | 1.0 (0.6, 1.3)     | 1.0 (0.6, 1.4)     | 0.8 (0.6, 1.2)         | 0.183   |
| INR [IU, median (IQR)]           | 1.1 (1.0, 1.3)     | 1.05(1, 1.1)       | 1.1 (1.0, 1.3)         | 0.266   |
| Albumin [g/dL, median (IQR)]     | 45.0 (39.7, 47.2)  | 45.0 (41.0, 50.0)  | 33.0 (31.0, 47.0)      | 0.036   |
| Bilirubin [umol/L, median (IQR)] | 13.0 (7.75, 22.2)  | 12.0 (8.0, 22.0)   | 14.0 (7.0, 26.0)       | 0.080   |
| MELD score* [median (IQR)]       | 8 (6, 10)          | 8 (7, 10)          | 7 (6, 10)              | 0.731   |
| MELD-Na score* [median (IQR)]    | 10 (7, 15)         | 11 (7, 15)         | 9 (6, 17)              | 0.940   |
| CTP score* [median (IQR)]        | 5 (5,5)            | 5 (5,5)            | 5 (5,7)                | 0.090   |

**Abbreviations:** Standard error (SE), hepatic encephalopathy (HE), alanine aminotransferase (ALT), aspartate aminotransferase (AST), international normalized ration (INR), model for end-stage liver disease (MELD), CLIF acute decompensation score (CLIF-AD), Child-Turcotte-Pugh (CTP).

\*Disease scores only calculated for cirrhotic patients.

**Table S2. Change in alcohol consumption across study period grouped by frequency of app use.**

|                                                         |                     | Number of login      |                   | p-value |
|---------------------------------------------------------|---------------------|----------------------|-------------------|---------|
|                                                         | (< 30 logins) n=18  | (30- 60 logins) n=9  | (>60 logins) n=14 |         |
| Baseline alcohol intake [g/week, median (IQR)]          | 303.2 (145.6-644.0) | 560.0 (433.6-1736.0) | 400.0 (0-756.0)   | 0.098   |
| 3-month alcohol intake [g/week, median (IQR)]           | 118.4 (28.8-384.0)  | 84.8 (0-771.2)       | 0 (0-205.6)       | 0.230   |
| Change in alcohol intake at 3-months [% , median (IQR)] | -49.1 (-94.9, 43.5) | -64.9(-100, 13.1)    | -100(-100, -55,1) | 0.124   |
| Abstinence at week 12 n (%)                             | 3(16.7)             | 3(33.3)              | 8(57.1)           | 0.057   |
| Number of alcohol re-admission after study n (%):       |                     |                      |                   | 0.188   |
| 0                                                       | 13(72.2)            | 5(55.6)              | 12(85.7)          |         |
| 1                                                       | 2(11.1)             | 2(22.2)              | 2(14.3)           |         |
| 2                                                       | 0                   | 1(11.1)              | 0                 |         |
| >=3                                                     | 3(16.7)             | 1(11.1)              | 0                 |         |

**Table S3. Logistic regression for abstinence in participants completing the study.**

|                      | Univariable |              |       |  | Multivariable |             |       |
|----------------------|-------------|--------------|-------|--|---------------|-------------|-------|
|                      | OR          | 95%CI        | P     |  | OR            | 95%CI       | P     |
| Sex(male)     | 0.286       | 0.051-1.592  | 0.153 |  | 0.210         | 0.020-2.173 | 0.191 |
| Age           | 0.983       | 0.929-1.040  | 0.555 |  |               |             |       |
| Cirrhosis     | 1.765       | 0.375-8.315  | 0.473 |  |               |             |       |
| MELD score    | 1.198       | 0.934-1.537  | 0.155 |  | 1.164         | 0.897-1.510 | 0.253 |
| CTP score     | 1.622       | 0.641-4.104  | 0.307 |  |               |             |       |
| Logins >60 | 2.692       | 0.675-10.740 | 0.161 |  | 1.812         | 0.322-10.2  | 0.500 |

Variables with p< 0.2 in univariable analysis were selected for inclusion in multivariable analysis.  
Method: backward, condition.

**Table S4. Alcohol consumption data of participants completing baseline and 3-month visits, with compliance threshold at 37 logins.**

| Alcohol intake                                          | Overall              | Non-compliant group  | Compliant group        | P-value |
|---------------------------------------------------------|----------------------|----------------------|------------------------|---------|
|                                                         | n=41                 | (<37 logins) n=19    | (>=37 logins) n=22     |         |
| Baseline alcohol intake [g/week, median (IQR)]          | 448.0 (156.9, 731.2) | 350.0 (184.8, 610.0) | 644.0 (388.0, 936.0)   | 0.172   |
| 3-month alcohol intake [g/week, median (IQR)]           | 678.4 (0, 384.0)     | 119.9 (30.0, 384.0)  | 32.8 (0, 331.2)        | 0.991   |
| Change in alcohol intake at 3-months [% , median (IQR)] | -75.49 (-100, -8.3)  | -57.1 (-91.4, -1.3)  | -100.0 (-100.0, -39.8) | 0.039   |
| Abstinence at week 12 of therapy [n (%)]                | 14 (34.1)            | 3 (15.8)             | 11 (50.0)              | 0.021   |
| Readmission rate [n (%)]                                | 10(24.4)             | 5(26.3)              | 5(22.7)                | 0.790   |

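### The binary rows of Table S3 imply 23 events among the 41 completers, but Tables S2 and S4 report 14 abstinent; separately, the overall 3-month median in Table S4 is impossible

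*Combined protocol and SAP*

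**What the plan says.** Table S3 is titled "Logistic regression for abstinence in participants completing the study". Its univariable columns (OR, 95% CI, P) read "0.286 | 0.051-1.592 | 0.153" for male sex, "1.765 | 0.375-8.315 | 0.473" for cirrhosis and "2.692 | 0.675-10.740 | 0.161" for more than 60 logins. The multivariable entry for logins is "1.812 | 0.322-10.2 | 0.500". A footnote says that variables with univariable P below 0.2 went forward to a backward selection. Table S3 gives no time point or definition for abstinence.

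Table S2 has a row labelled "Abstinence at week 12 n", with 3 of 18, 3 of 9 and 8 of 14 in the three login groups; the highest group is headed ">60 logins) n=14". Table S4 labels its row "Abstinence at week 12 of therapy [n" and gives 14 of 41 overall, split 3 of 19 and 11 of 22 at a 37-login threshold.

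Table S4 also gives 3-month intake in g/week as median 678.4 (IQR 0 to 384.0) overall, 119.9 (30.0 to 384.0) below 37 logins and 32.8 (0 to 331.2) at or above 37 logins.

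**The concern.** Tables S2, S3 and S4 describe the same 41 completers and appear to describe the same outcome. If so, the Table S3 odds ratio for >60 logins should follow directly from the Table S2 counts. It does not. Table S3 is the only place where the link between device use and abstinence is adjusted for anything, and protocol section 4 says that the findings on intake, compliance and acceptability will determine whether a randomised trial is feasible. A reader who uses Table S3 for that purpose would be relying on an association with an outcome other than the one tabulated beside it.

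The Table S4 cell is a separate matter. It is the overall 3-month summary of the primary outcome, and as printed it cannot be a median of these data.

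**Working it through.** **Method.** Univariable logistic regression on a binary predictor gives the 2x2 odds ratio with a Wald interval. With a of n1 events in the exposed group and c of n0 in the other, b = n1 − a and d = n0 − c:

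OR = ad/(bc); SE = √(1/a + 1/b + 1/c + 1/d); CI = exp(ln OR ± 1.96 SE); z = ln OR/SE.

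**Inputs.** From the completers column of Table S1: 32 male and 9 female; 9 with cirrhosis and 32 without. From Table S2: 14 with >60 logins and 18 + 9 = 27 with 60 or fewer.

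**Step 1: reproduce Table S3.** Every possible pair of event counts was tried at these group sizes, and at every smaller subset to allow for missing data. Each row has one match:

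| Row | Events | OR | SE | 95% CI | P | Total events |
|---|---|---|---|---|---|---|
| Male | 16/32 v 7/9 | 16×2/(16×7) = 0.286 | √(1/16+1/16+1/7+1/2) = 0.876 | 0.051–1.592 | 0.153 | 23 |
| Cirrhosis | 6/9 v 17/32 | 6×15/(3×17) = 1.765 | √(1/6+1/3+1/17+1/15) = 0.791 | 0.375–8.315 | 0.473 | 23 |
| >60 logins | 10/14 v 13/27 | 10×14/(4×13) = 2.692 | √(1/10+1/4+1/13+1/14) = 0.706 | 0.675–10.740 | 0.161 | 23 |

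All three agree with print to rounding, and all three give 23/41 = 56.1%.

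**Step 2: check that 14 is not a misprint.** Table S2 sums to 3 + 3 + 8 = 14 and Table S4 to 3 + 11 = 14; 14/41 = 34.1%. Pearson chi-square gives P=0.057 for 3/18, 3/9, 8/14 and P=0.021 for 3/19 v 11/22. Both are the printed values, so 14 is the count behind both tables.

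**Step 3: try 14 events in Table S3.** At the printed group sizes the closest tables do not fit. For logins, 7/14 v 7/27 gives OR 2.857, P=0.129. For sex, the nearest OR is 0.313 (9/32 v 5/9). For cirrhosis, 4/9 v 10/32 gives OR 1.760, but the CI is 0.388–7.986. Reversing the outcome coding exchanges 23 events for 18, which is neither 14 nor 27.

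**Step 4: the login row from the Table S2 counts, 8/14 v (3+3)/27 = 6/27.**

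- OR = 8×21/(6×6) = 4.667.
- SE = √(1/8+1/6+1/6+1/21) = 0.711.
- CI = exp(1.540 ± 1.394) = 1.158 to 18.81.
- z = 1.540/0.711 = 2.17, Wald P=0.030.
- Fisher P=0.039; Pearson P=0.025.
- Continuity-corrected chi-square = 41×(|168 − 36| − 20.5)²/(14×27×14×27) = 3.57, P=0.059.

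**Step 5: the Table S4 median.** A median cannot exceed its own upper quartile, yet 678.4 > 384.0. The pooled median of 41 values is the 21st. At least 10 of the 19 values in one group and 11 of the 22 in the other are at or below 119.9, which makes 21, so the pooled median is at most 119.9. By the same count from above, at least 11 + 10 = 21 values are at or above 32.8. The median must therefore lie between 32.8 and 119.9. The printed figure is 678.4/119.9 = 5.66 times the upper limit.

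**The case against.** The best defence is that Table S3 says only abstinence, whereas Tables S2 and S4 say week 12, so Table S3 may use another legitimate definition. The documents leave that open, and the cause cannot be settled from them. But no second definition is given. One natural candidate, zero intake at 3 months, does not supply 23 events: in Table S4 a median of 32.8 in 22 people allows at most 11 zeros, and a lower quartile of 30.0 in 19 people allows about 4 or 5. An undefined outcome would itself need correcting.

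Taken alone, the login row can be fitted with 14 events, as 10/23 v 4/18. That needs 23 people with >60 logins, against 14 in Table S2, and it leaves the sex and cirrhosis rows unexplained. Some entries in Table S6 imply a 12/29 compliance split, but that split gives no match either.

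It is also fair to say that little rests on Table S3. Protocol section 9 plans correlation and linear regression for compliance, not a logistic model, and the unadjusted link with abstinence is visible in Tables S2 and S4. This stands: the point concerns reported supplementary results and is not a defect in the planned primary analysis.

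The 678.4 may be a decimal slip; 67.84, for example, would fall in the permitted range. That is an assumption, and the data must settle it.

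**Conclusion.** The discrepancy is established by arithmetic on printed figures: 23 events behind Table S3 against 14 in Tables S2 and S4. It assumes only that the univariable rows are ordinary logistic regressions with Wald intervals, and the exact agreement of three separate rows supports that. On the week-12 counts, the >60-login odds ratio moves from 2.69 (0.675 to 10.74) to 4.67 (1.16 to 18.8). The overall 3-month median in Table S4 is impossible as printed.

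Several stronger readings do not follow:

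- A reader might infer that the corrected result is the opposite of the printed one. Both estimates favour >60 logins, the intervals overlap widely, and each estimate lies inside the other interval. Only nominal significance changes, and that depends on the test (0.030, 0.039 or 0.059).
- A reader might take Table S3 as showing that device use is unrelated to abstinence. It makes no such statement, and an interval reaching 10.7 is inconclusive.
- A reader might take the corrected figure as evidence that the device works. Login frequency was not randomised, and there are only 14 events.
- A reader might conclude that the multivariable odds ratio of 1.812 is wrong by a known amount. It cannot be checked without patient data. Even its sample size is unclear, because Table S1 says that disease scores were calculated only for cirrhotic patients (9 completers) and the model includes MELD.
- Read literally, Table S4 suggests that intake rose from 448.0 to 678.4. Its own quartiles and the printed median change of −75.49% contradict this.

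**What to change.** 1. Identify the variable used in Table S3. Either refit the whole table on the 14-event week-12 abstinence variable of Tables S2 and S4, or rename and define the Table S3 outcome and explain why it has 23 events where those tables have 14.
2. If it is refitted, repeat the P<0.2 screening and the multivariable model on the same outcome, since the variables selected may change. State the number of participants and events in each model, including how MELD was obtained for participants without cirrhosis.
3. Recompute the overall 3-month median in Table S4 from the data.

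The cost is re-running two tables from data already held, and issuing a correction to reported supplementary results. No new data are needed, and the planned primary analysis does not change.

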**Table S5. Demographic characteristics of participants sampled for qualitative evaluation.**

| Baseline characteristic
[units] | Range                         | n (%) |
|--------------------------------------------|--------------------------------------|--------------|
| Age range [year]                           | 35 to 44                             | 1 (14.3)     |
|                                            | 45 to 54                             | 3 (42.9)     |
|                                            | 55 to 64                             | 2 (28.6)     |
|                                            | 65 to 74                             | 1 (14.3)     |
| Sex [male n (%)]                           | -                                    | 5 (71.4)     |
| Average weekly alcohol [units]             | 0                                    | 5 (71.4)     |
|                                            | 1 to 7                               | 0            |
|                                            | 8 to 14                              | 1 (14.3)     |
|                                            | 15 to 21                             | 0            |
|                                            | 22 to 28                             | 1 (14.3)     |
| Occupational status                        | Employed                             | 4 (57.1)     |
|                                            | Unemployed                           | 2 (28.6)     |
|                                            | Retired                              | 1 (14.3)     |
| Education level                            | Not completed
higher
education | 2 (28.6)     |
|                                            | Completed
higher
education     | 5 (71.4)     |

**Table S6. Education, Socio-economic status and Support USers To Access Information and Services (SUSTAINS) questionnaire data.**

| Questionnaire data                                                                  | Overall              | Non-compliant group    | Compliant group           | p-value |
|-------------------------------------------------------------------------------------|----------------------|------------------------|---------------------------|---------|
|                                                                                     | n=41                 | n=29                   | n=14                      |         |
| Education                                                                    |                      |                        |                           | 0.873   |
| Less than university                                                                | 23 (56.1)            | 17 (58.62)             | 6 (50)                    |         |
| University or higher                                                                | 18 (43.9)            | 12 (41.38)             | 6 (50)                    |         |
| GP visit                                                                     |                      |                        |                           | 1       |
| >= once per month                                                                   | 23 (56.1)            | 16 (55.17)             | 7 (58.33)                 |         |
| < once per month                                                                    | 18 (43.9)            | 13 (44.83)             | 5 (41.67)                 |         |
| Deprivation rank                                                             | 16989.79 (1181.12)   | 17312.48 (1513.99)     | 16263.75 (1844.80)        | 0.664   |
| Deprivation decile                                                           | 5.62 (0.36)          | 5.78 (0.46)            | 5.25 (0.57)               | 0.509   |
| Income rank                                                                  | 15169.77 (1147.40)   | 15600.63 (1408.52)     | 14200.33 (2026.49)        | 0.576   |
| Income decile                                                                | 5.15 (0.35)          | 5.26 (0.42)            | 4.92 (0.62)               | 0.653   |
| Income score                                                                 | 0.12 (0.01)          | 0.12 (0.01)            | 0.13 (0.02)               | 0.688   |
| Employment rank                                                              | 18201.64 (1338.36)   | 18371.74 (1700.49)     | 17818.92 (2170.90)        | 0.843   |
| Employment decile                                                            | 6 (4,9)              | 6 (4,9)                | 5.5 (4,8)                 | 0.747   |
| Employment score                                                             | 0.08 (0.04, 0.1)     | 0.08 (0.04, 0.1)       | 0.08 (0.05, 0.1)          | 0.843   |
| Education rank                                                               | 27355 (20311, 30218) | 27355 (19173.5, 30218) | 27291 (23777.25, 29521)   | 0.879   |
| Education decile                                                             | 9(6,10)              | 9(6,10)                | 9(8,9)                    | 0.790   |
| Health rank                                                                  | 23127.90 (1108.53)   | 22933.81 (1403.60)     | 23564.58 (1814.98)        | 0.786   |
| Health decile                                                                | 8(6,9)               | 8(6,9)                 | 8(6,10)                   | 0.734   |
| Crime rank                                                                   | 12759.00 (1082.64)   | 13633.67 (1487.36)     | 10791.00 (941.25)         | 0.115   |
| Crime decile                                                                 | 4(3,6)               | 4(3,7)                 | 4(3,4)                    | 0.247   |
| Housing rank                                                                 | 10670.69 (917.85)    | 10917.70 (1183.19)     | 10114.92 (1404.53)        | 0.666   |
| Housing decile                                                               | 3.67 (0.28)          | 3.74 (0.37)            | 3.50 (0.40)               | 0.661   |
| Environment rank                                                             | 7684 (5547, 13088)   | 8336 (6065.5, 11971.5) | 5952.5 (4868.25, 13332.5) | 0.394   |
| Environment decile                                                           | 3(2,4)               | 3(2,4)                 | 2(2,4.75)                 | 0.446   |
| How long does it take you to reach to the closest primary care centre? n (%) |                      |                        |                           | 0.337   |
| No answer                                                                           | 4 (9.76)             | 4 (13.79)              | 0 (0)                     |         |
| 15 minutes                                                                          | 22 (53.66)           | 15 (51.72)             | 7 (58.33)                 |         |
| 15-30 minutes                                                                       | 12 (29.27)           | 9 (31.03)              | 3 (25)                    |         |

|                                                                               |            |            |           |       |
|-------------------------------------------------------------------------------|------------|------------|-----------|-------|
| 30-60 minutes                                                                 | 3 (7.32)   | 1 (3.45)   | 2 (16.67) |       |
| How long does it take you to reach to your general practitioner? n (%) |            |            |           |       |
| No answer                                                                     | 4 (9.76)   | 4 (13.79)  | 0 (0)     | 0.573 |
| 15 minutes                                                                    | 22 (53.66) | 15 (51.72) | 7 (58.33) |       |
| 15-30 minutes                                                                 | 12 (29.27) | 8 (27.59)  | 4 (33.33) |       |
| 30-60 minutes                                                                 | 1 (2.44)   | 0 (0)      | 1 (8.33)  |       |
| 1-2 hours                                                                     | 1 (2.44)   | 1 (3.45)   | 0 (0)     |       |
| More than 2 hours                                                             | 0          | 0          | 0         |       |
| Don't know                                                                    | 1 (2.44)   | 1 (3.45)   | 0 (0)     |       |
| How long does it take you to reach to closest hospital? n (%)          |            |            |           | 0.387 |
| No answer                                                                     | 4 (9.76)   | 4 (13.79)  | 0 (0)     |       |
| 15 minutes                                                                    | 10 (24.39) | 5 (17.24)  | 5 (41.67) |       |
| 15-30 minutes                                                                 | 14 (34.15) | 11 (37.93) | 3 (25)    |       |
| 30-60 minutes                                                                 | 12 (29.27) | 8 (27.59)  | 4 (33.33) |       |
| 1-2 hours                                                                     | 1 (2.44)   | 1 (3.45)   | 0 (0)     |       |
| More than 2 hours                                                             |            | 0          | 0         |       |
| Don't know                                                                    |            | 0          | 0         |       |

